##### Sample size justification and power calculations

We require a sufficient sample to detect non-inferiority based on a clinically significant change of 5 points on the PCL [101, 102]. Calculations of a design effect (measure of how the design effects the standard error of the parameters) [103, 104] accounted for clustering. We computed intraclass correlations (ICC) with repeated observations of CPT patients at the clinic (*ρ* = 0.12), clinician (*ρ* = 0.16), and patient (*ρ* = 0.38) level in our prior research in Canada and VA, yielding a design effect of up to 2.32 [83]. Power to detect a clinically meaningful difference on PTSD symptom scores over time, taking the design effect into account, is .80 in a two-sided test, using repeated measures, with an alpha-level of 0.05 and a standard deviation (sd) of 7 points (based on prior research), for a sample size during the IS phase of 288 patients (144 per condition) within 32 clusters. In the proposed study, we expect to randomize 32 clinics, with an average of three clinicians per clinic and at least four patients per clinician during both the IS and follow-up phase. For each patient, PTSD symptoms will be measured at nine time points, as it is typical to assess symptoms frequently in CPT (baseline, every other session, post-treatment, and follow-up). To very conservatively account for potential patient-level attrition and missing data during treatment, we estimated an average of four observations per patient. Furthermore, we considered the longer study length, rates of turnover in each system, attrition rate in previous studies, balanced with participation in an active intervention, system support, and incentives, to anticipate substantial, but not unmanageable, attrition. Full participation in the IS and follow-up would yield 384 patients and at least 1536 observations, and thus, we could see a clinician attrition rate of 33% while remaining adequately powered to detect non-inferiority of CQI, and superiority of the ISs as compared to the baseline/non-IS phase data (an additional 2 patients per clinician; up to 192 patients). This projection exceeds the rate of attrition seen in our prior studies in these systems and is sufficient to test for non-inferiority on OQ measure as a secondary analysis, as the OQ-45 has an RCI of 14 (sd = 16) [105]. Finally, the sample will allow for a stable estimate of a fidelity based on the recommended *G* = .70–.80 level of dependability) [106].

3.I.5 Testing of additional hypotheses and exploratory analyses. To compare the budgetary impact of each IS (hypothesis 2), a budget impact analysis (BIA) [107] will be conducted to estimate the cost to the system of implementing and sustaining each IS. Results will be interpreted in conjunction with the findings for hypothesis 1A. If evidence of non-inferiority is found, the less expensive IS may be warranted, but significant differences in favor of the more costly IS might justify the added expense.

Hypotheses 3–7 involve continuous outcome data and will employ a similar multilevel regression strategy as described in section 3.I.1. We will also examine interactions between these variables and ISs to assess for a moderating effect on patient outcomes and will similarly explore potential moderating effects of attitudes (EBPAS) and social context (OSC) and leadership (ILS) on the key outcomes of interest. We will explore whether the system impacts the effects of the ISs by testing interactions between system, IS, and time.

##### Aim 2

The second aim is to assess each IS’s acceptability and perceived fit in diverse mental health systems.

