### Summary of the proposed project

Clinics in three mental health systems that have implemented CPT for PTSD will submit baseline session recordings and patient data for at least two patients (*n* = 192) before random assignment to either 12 months of FID (*n* = 16 clinics, 48 clinicians, 192 patients), or CQI (*n* = 16 clinics, 48 clinicians, 192 patients). Outcomes will include patient self-reported PTSD symptom outcomes (primary); independent fidelity ratings; and penetration, adaptation, and capacity to deliver CPT [46, 69]. We will also investigate engagement in, credibility and costs of, and satisfaction with each IS [mechanisms by which the interventions impact patient outcomes] as well as contextual factors that may impact sustainability. The mixed method design will include qualitative methods for a richer understanding of the process and outcomes for each of the ISs [70]. This study will capitalize on infrastructure created for a previous trial comparing EBP consultation strategies [59] as well as existing infrastructure in the participating mental health systems and strong collaborative relationships and experience with each participating mental health system. The study has the potential to advance implementation science beyond observational studies of EBP sustainability by providing much-needed information on the effectiveness of interventions to promote long-term EBP implementation.

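### The stated tolerance of 33% clinician attrition contradicts the plan's own figures: going from 384 patients to the required 288 allows a loss of 25%

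*Protocol article*

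**What the plan says.** All the figures stand in one paragraph of the protocol article, under Sample size justification and power calculations.

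- **Requirement.** Power "is .80 in a two-sided test, using repeated measures", and this is stated "for a sample size during the IS phase of 288 patients (144 per condition) within 32 clusters".
- **Expected enrolment.** The investigators write that "we expect to randomize 32 clinics, with an average of three clinicians per clinic and at least four patients per clinician". From this they conclude: "Full participation in the IS and follow-up would yield 384 patients and at least 1536 observations". The section Summary of the proposed project gives matching numbers per arm: "FID (*n* = 16 clinics, 48 clinicians, 192 patients", and the same for continuous quality improvement (CQI).
- **Tolerance.** Directly after the 384, and as its consequence, the paragraph says "we could see a clinician attrition rate of 33% while remaining adequately powered to detect non-inferiority of CQI". It extends the claim to superiority of both implementation strategies (ISs) over the no-intervention phase.
- **Reassurance.** The paragraph expects attrition to be substantial. It treats the projection as safe because it lies above the attrition seen in earlier studies in these systems. That earlier rate is not given.

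Patient-level dropout is handled separately, by counting only four observations per patient (384 × 4 = 1536). It is not part of the 33%.

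**The concern.** Attrition is a loss from those enrolled, so the tolerable rate has to be measured against 384. A rate of 33% applied to 384 gives a number below 288, and the paragraph names no smaller sample as adequate. The premise and the conclusion therefore disagree.

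This sentence is the article's only stated allowance for clinician attrition in the primary non-inferiority comparison, and it is the yardstick against which prior attrition is judged acceptable. With the yardstick at 33%, a loss anywhere between 25% and 33% would be read as harmless although the stated sample had been missed. Because the prior rate is not printed, a reader cannot tell whether it also lies below 25%.

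**Working it through.** **Inputs, all from the sample size section:** required 288 patients (144 per condition) in 32 clinics; 3 clinicians per clinic; 4 patients per clinician; clinic-level intraclass correlation 0.12; design effect up to 2.32; two-sided alpha 0.05; power 0.80; difference 5 points; SD 7.

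**1. Expected enrolment.** 32 × 3 = 96 clinicians and 96 × 4 = 384 patients. This reproduces the plan's figure.

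**2. Reproducing the 33%.** The surplus is 384 − 288 = 96. Divided by the required number, 96/288 = 33.3%. This matches the printed figure, but the base is wrong for an attrition rate. That the figure arose in this way is inferred from the match, since the article shows no derivation.

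**3. Tolerance on the right base.** (384 − 288)/384 = 96/384 = 25.0%, which is 24 of 96 clinicians if leavers contribute no patients.

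**4. What 33% leaves.** 384 × 0.67 = 257.3. With exactly one third gone, 64 clinicians × 4 = 256, or 128 per arm against 144. The shortfall is 31 to 32 patients, about 11% of 288. Keeping 288 after a 33% loss would need 288/0.67 ≈ 430 enrolled.

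**5. Power at 257, taking 288 as the number that gives 0.80.** Power = Φ(2.80 × √r − 1.96), where 2.80 = 1.96 + 0.84 and r is the ratio of effective sample sizes (patients divided by design effect). The clinic-level design effect is 1 + (m − 1) × 0.12 for m patients per clinic: 2.32 at m = 12, 1.96 at m = 9, and about 1.845 at m = 257/32 ≈ 8.

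| Assumption | r | Power at 257 |
|---|---|---|
| Design effect unchanged | 257/288 = 0.892 | about 0.75 |
| 288 sized at 9 per clinic; all 32 clinics stay | (257/1.845)/(288/1.96) = 139.3/146.9 = 0.948 | about 0.78 |
| 288 sized with 2.32 (12 per clinic); all 32 clinics stay | (257/1.845)/(288/2.32) = 139.3/124.1 = 1.122 | about 0.84 |

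**6. Where 288 comes from.** The plain two-sample formula with difference 5 and SD 7 gives 31 per arm. Times 2.32 this is 72 per arm, 144 in total, not 288. A change-score SD of 7 × √2 = 9.9, which is an assumption because the article does not state it, gives 62 per arm. Times 2.32 this is 143.8 per arm, about 288 in total. So the basis of 288 is not clear from the printed inputs. With SD 7 and design effect 2.32, 257 patients would have about 0.96 power.

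**The case against.** Three arguments favour the plan.

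- **Clinicians are not patients.** A clinician who leaves partway may already have enrolled patients. If 32 of 96 leave after one patient each on average, the total is 64 × 4 + 32 × 1 = 288, exactly the requirement. This stands as a limit on the 25%, which assumes that leavers contribute nothing.
- **The 384 uses low inputs.** The section Recruitment plans 3 to 4 clinicians per clinic, and four patients per clinician is given as a minimum. At 3.5 per clinic, 112 × 4 = 448, and a 33% loss leaves 300. This shows that the margin may be wider in practice, but the power paragraph and the project summary both use three.
- **Smaller clusters lower the design effect.** If clinicians leave and clinics remain, power at 257 may stay above 0.80, as the last row of the table shows. This stands too.

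None of these rescues the sentence as printed. The article uses none of them to support 33%; it derives the tolerance from 384 and 288 alone.

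A reader might go further and infer that the trial would be underpowered at 33% attrition. The documents do not support that: the answer runs from about 0.75 to 0.84 with the design effect, and the printed SD alone would give more. A reader might also infer that the 384 are spread over the IS year and the follow-up year, so that the IS phase falls short of 288 even without attrition. The wording on phases is loose, but an even split is nowhere stated. Summary of the proposed project attaches 192 patients per arm, 384 in all, to the 12-month strategies, which speaks against it.

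**Conclusion.** The point holds as an internal inconsistency. On the article's own 288 and 384, the tolerable clinician loss is 25%, not 33%, and a 33% loss ends about 31 patients below the stated requirement. This rests on two assumptions: that 288 and 384 count patients in the same phase, and that a clinician who leaves takes all four patients along. Whether power would in fact fall below 0.80 cannot be settled from the article, because it depends on the cluster size behind the design effect and on the unexplained basis of 288. Since the plan relies on the figure to call expected attrition safe, and restating it is cheap, it should be corrected.

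**What to change.** - Replace 33% with 25% (24 of 96 clinicians, if leavers contribute no patients). Alternatively, keep 33% and show the calculation that supports it, including the design effect at the reduced number of patients per clinic and any patients already enrolled by leavers.
- Repeat the comparison with attrition in the earlier studies against the corrected figure, and print the earlier rate.
- State that 288 and 384 refer to the same phase, or give the expected number for each phase.

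The cost is one figure and a sentence or two, with no change to the design. The stated safety margin becomes less favourable.

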## Methods

### Summary

We plan to randomize clinics and associated clinicians in three mental health systems that have implemented CPT for at least 2 years into one of two conditions: CQI-LC or FID. Implementation outcomes will be assessed. ISs will be compared over the course of the 1-year intervention phase and a 1-year follow-up. Mechanisms of action and budget impact will also be explored. A phased rollout of the ISs will allow baseline data to serve as within and across subject comparison data. Potential individual and contextual influences on sustainability will also be assessed through surveys and interviews to elucidate how these factors may impact CPT delivery and IS engagement and outcomes.

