### Inclusion/exclusion criteria

We will recruit VAC and VA clinics, TX, and Canadian community clinics that participated in CPT training and have at least 4 clinicians eligible to participate. Clinics are defined as work units under the same supervisor or service line within an organization. Clinicians and supervisors who maintain a caseload will be eligible to participate in the study if they (1) are CPT-trained and provide psychotherapy to individuals with PTSD, (2) are willing to record therapy sessions, provide work samples for baseline assessment, and complete baseline surveys, and (3) have internet access. We considered only enrolling clinicians who had achieved a certain level of CPT adherence (e.g., “provider status”) but recognized that stakeholders need to understand how to improve EBP delivery among *all* clinicians who deliver EBPs within the system, including the 23–47% of clinicians (Table 1) who receive training but do not achieve provider status. Their inclusion allows assessment of ISs’ ability to improve capacity to deliver high quality CPT.

Eligible patient participants are Veterans or non-Veterans (1) diagnosed by their clinicians to have current PTSD, with a minimum PTSD checklist (PCL) score of 33 (based on the most current validation and cutoff scores that indicate a likely PTSD diagnosis for the PCL-5) [71] 2) who have not previously received CPT, and (3) are willing to consent to completing symptom measures and have their sessions audio recorded and reviewed. Patients are permitted to continue other psychotherapies if the treatment is not specifically focused on PTSD. Ineligible patients are those ineligible for CPT based on the state of research evidence as follows: (1) current uncontrolled psychotic or bipolar disorder, (2) [past month] substance dependence requiring daily use or detoxification (eligibility can be revisited if individuals enter recovery), (3) imminent suicide/homicide risk requiring immediate intervention, and (4) cognitive impairment precluding therapy engagement (e.g., significantly impaired memory or attention).

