#### Analytic strategy

We will examine descriptive statistics and distribution of all variables. Outcome variables will be transformed as needed if data violate assumptions of normality. We will evaluate effectiveness of randomization by comparing baseline measures of the key variables and demographics using χ^2^ and *t* tests.

##### Aim 1

The first aim is to examine the impact of two LC interventions for sustained EBP delivery on the use and effectiveness of CPT. We will test hypothesis 1A (non-inferiority of FID relative to CQI) by examining [95] whether the difference in change between the groups after the ISs is complete (12 months) and at follow-up is smaller than a predetermined clinically reliable difference (i.e., the non-inferiority margin “delta”).

To estimate change, we will use multilevel regression (i.e., growth curve analyses, mixed effect regression, hierarchical linear modeling), which offers numerous strengths for analyzing change over time for nested data, including efficiency in handling missing data, powerful and accurate estimation procedures adjusting for clustering, and modeling flexibility (e.g., allows for the inclusion of continuous or categorical, time invariant or time varying, covariates and predictors). This approach is extremely robust to missing data and considered “state of the art” for analyzing unbalanced data sets due to dropouts and loss to follow-up [96].

A three-level model will be evaluated to test the impact of IS on change in PTSD. Time (since pre-treatment) will be entered as a level-1 predictor to estimate change in PCL-5 scores. Level 2 will be included to account for the individual assessments nested within patients. Since randomization occurred at the clinic level, IS (dummy coded variable) will be entered as a level-3 predictor to examine the impact of IS on change over time in PTSD symptoms. Given the small number of systems, system will be a level-3 (clinic level) variable to assess and adjust for its influence. We will examine the influence of potentially significant covariates (e.g., baseline PCL-5, VA vs. community; veteran status, other clinician, or patient characteristics/diagnoses) and include in analyses if necessary.

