To examine hypothesis 1B (that both ISs will be superior to no intervention), we will conduct piecewise multilevel growth modeling, which will allow us to estimate separate trajectories for each phase of the study by condition. This approach is being increasingly used in randomized controlled trials to more clearly elucidate change across multiple phases [97].

To further compare the impact of the ISs to no intervention (hypothesis 1B), we will use PCL and diagnostic data extracted from VAC’s CROMIS and the VA records. We will separately examine administrative PCL data for all patients with PTSD seen by VAC and VA clinicians through CROMIS and VA’s clinical CPT templates and clinical reminder data, both of which have capacity for clinic and clinician-level linkage and data extraction.

Hypothesis 1C. Different mechanisms of change will be evident for the two ISs. We hypothesize that FID will impact outcomes through increased fidelity and that CQI will impact outcomes through adaptation and development of learning organizations. Lagged regression modeling is a useful way to examine temporal precedence between contemporaneous time-varying phenomena, where a causal effect of variable X1 on X2 is established when X1 at time 1 significantly contributes to the behavior of X2 at time 2 while controlling for the effect of X2 at time 1 [98, 99]. To evaluate temporal precedence, lagged multivariate multilevel models will be evaluated [100]. Multivariate models will allow for the inclusion of two outcomes in the same model [100]. Each of the outcomes will be predicted by the level of that outcome at the previous time point (i.e., autoregressive effect, e.g., PTSD at time 2 will be predicted by PTSD at time 1) and the other variable (observer-rated fidelity, adaptation, or LOS score) in the model at the previous assessment occasion (i.e., cross-lagged path PTSD will be predicted by the proposed mechanism and vice-versa). We will also account for overall increases and decreases in the model by including time as a predictor of each outcome.

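### Hypothesis 1B can mistake a change in which clinicians contribute patients for an effect of the strategies; the phase contrast should be made within clinicians

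*Protocol article*

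**What the plan says.** **Benchmark.** The sample size section sets the no-IS data at "an additional 2 patients per clinician; up to 192 patients". Summary of the proposed project places these data before random assignment. Under Inclusion/exclusion criteria, clinicians may enter only if they "are willing to record therapy sessions, provide work samples for baseline assessment, and complete baseline surveys". Clinicians who later leave can therefore be in the benchmark.

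**IS phase.** The sample size section expects 32 clinics, an average of three clinicians per clinic and at least four patients per clinician. On loss it says: "we could see a clinician attrition rate of 33% while remaining adequately powered to detect non-inferiority of CQI, and superiority of the ISs". It adds that this rate is higher than the investigators have seen in these systems.

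**Analysis.** Under Analytic strategy, 1B is tested by "piecewise multilevel growth modeling, which will allow us to estimate separate trajectories for each phase of the study by condition". No levels are given for that model. The only levels stated are those of the three-level model set out for 1A: time at level 1, then "Level 2 will be included to account for the individual assessments nested within patients", and clinic at level 3. Clinician characteristics are optional covariates.

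**Intention.** The Methods summary says: "A phased rollout of the ISs will allow baseline data to serve as within and across subject comparison data".

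**The concern.** The two sides of the 1B contrast need not come from the same clinicians. A clinic term removes differences between clinics but not a change in the mix of clinicians inside a clinic. If those who stop differ in effectiveness from those who stay, a clinic's average PCL-5 change moves between phases even when no clinician's results have changed. The protocol's robustness claim for multilevel models concerns incomplete data in the model. Patients whom a departed clinician never enrolled are not missing assessments.

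Effectiveness is likely to vary, because the trial deliberately admits clinicians who never reached provider status, and the quoted clinician ICC (0.16) exceeds the clinic ICC (0.12). The background links fidelity support to lower staff turnover and CQI to greater burden, so loss could also differ between arms and affect their separate 1B trajectories. 1B is the only hypothesis that compares the strategies with no strategy on symptoms.

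**Working it through.** **1. The plan's own counts**
- Clinicians: 32 × 3 = 96. Benchmark: 96 × 2 = 192. IS phase at full participation: 96 × 4 = 384. All agree with the text.
- Design effect: 1 + (12 − 1) × 0.12 = 2.32, as stated.
- Required 288: the inputs are a 5-point difference, "alpha-level of 0.05 and a standard deviation (sd) of 7 points", and power that "is .80 in a two-sided test, using repeated measures". With SD 7 the unclustered size is 31 per arm, and 31 × 2.32 = 72. The stated 144 per arm appears if the SD of a change score is taken as 7 × √2 = 9.9 (my assumption): 62 × 2.32 = 143.8.
- Tolerable loss: 1 − 288/384 = 25%. The stated 33% equals 384/288 − 1. Losing 33% leaves 0.67 × 384 = 257 patients, below 288.

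**2. Size of the shift, by formula**

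Assume no true IS effect, patient-level change SD 7, a fraction *a* of clinicians leaving before giving IS patients, and a correlation *r* between effectiveness and staying. The protocol's ICCs come from repeated observations; applying them to change is an assumption. For clinician SD *s*:

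shift = r × s × φ(z_a) / (1 − a)

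The text leaves two readings of the clinician ICC:
- 0.16 includes the clinic part: share 0.16 − 0.12 = 0.04, s = 7 × √0.04 = 1.4.
- 0.16 is all clinician: s = 7 × √0.16 = 2.8.

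At a = 1/3, φ(z_a)/(1 − a) = 0.545. For r = 0.3 and 0.5 the shift is 0.23 and 0.38 points (s = 1.4), or 0.46 and 0.76 (s = 2.8). At a = 25% the ranges are 0.18 to 0.30 and 0.36 to 0.59.

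**3. Simulation with a clinic term**

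32 clinics × 3 clinicians; 2 baseline and 4 IS patients per clinician; one change score per patient; clinic variance 0.12 × 49; clinician variance 0.04 × 49 or 0.16 × 49; remainder residual; zero IS effect; one third leave. The phase effect is estimated within clinic, with a nominal two-sided 5% test.

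| Clinician share | r | IS patients from leavers | Spurious effect (points) | False rejection |
|---|---|---|---|---|
| 0.04 | 0.3–0.5 | none | 0.2–0.3 | 6–7% |
| 0.04 | 1 (perfect selection) | none | 0.6 | 16% |
| 0.16 | 0.3–0.5 | none | 0.4–0.6 | 10–17% |
| either | 0.3–0.5 | half (2 each) | 0.2 or less | about 5–8% |
| either | 0 | none | 0 | about 5% |

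The simulated shifts fall below the formula because the clinic term absorbs part of the selection. The sign reverses if stronger clinicians leave.

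**4. What removes it**

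Share 0.16, no IS patients from leavers:

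| Model | r = 0.5 | r = 1 |
|---|---|---|
| Clinic term only | 0.62 | 1.37 |
| Plus clinician random effect | 0.39 | 0.95 |
| Clinician fixed effects | about 0 | about 0 |

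The random effect removes only part of the bias, because it still uses comparisons between clinicians. The within-clinician contrast kept false rejection near 5% in every scenario.

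**The case against.** - **The 1B levels are not stated.** The three-level model is described for 1A, and an article may leave the structure of the 1B model to the analysis plan. A reader might infer that the plan rules out a clinician term; it does not. The point survives because adding a clinician random effect, the usual choice, would leave more than half of the bias in step 4.
- **33% is a ceiling.** A reader might take it as the expected loss. The text offers it as tolerable and above past experience, and 384 to 288 is only 25%. Both stand, so the one-third scenario is towards the upper end. Anyone who leaves part-way may already have supplied IS patients, which brings the error rate close to nominal.
- **Direction.** It is tempting to say that weaker clinicians leave and that the strategies are flattered. No section says who leaves, and the bias could equally hide a benefit.
- **Larger error rates.** Giving leavers a deficit of 2.8 points while reading the ICC as cumulative yields about 20% false rejection. That reading does not allow it: the within-clinic clinician SD is 1.4, and losing exactly the weakest third separates leavers from stayers by 1.64 × 1.4 = 2.3 points.
- **Benchmark completeness.** The figure is a maximum and entry requires only willingness, so not every clinician need be represented.
- **Other comparisons.** The randomized delayed-start comparison is a real strength, but its baseline also includes clinicians who may leave later. The administrative data would keep clinicians who merely stop submitting and can be linked by clinician. They cover only two of the three systems (11 + 11 = 22 of the 32 planned clinics) and are analysed separately.

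**Conclusion.** The concern holds as a risk of bias in either direction, conditional on clinician loss being related to effectiveness. The unequal clinician sets follow from the design, and nothing stated for 1B corrects for them. With one third leaving before giving IS patients, SD 7 and a selection correlation of 0.3 to 0.5, the effect is modest under the cumulative ICC reading and material under the other. With unrelated loss there is no bias. If the change-score SD is 9.9, the shifts in points grow by √2 and the rejection rates do not change. The documents do not support the claim that 1B will be falsely declared, or that a third of clinicians are expected to leave. They do support fixing the contrast in advance, because the protection is cheap and choosing it after seeing who left would be open to criticism.

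**What to change.** In the 1B model, add a clinician level and separate the within-clinician phase effect, either with phase centred at the clinician mean or with clinician fixed effects. A clinician random intercept alone is not enough. Keep study period in the model, so that the randomized immediate versus delayed-start comparison is retained and the result does not rest on before-after change only. Report the all-clinician contrast beside it, and compare baseline PCL-5 change between clinicians who stayed and those who left. Correct the tolerable attrition to 25%, or show how 33% was obtained.

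Cost: wording only, since the fidelity and capacity outcomes already require clinician identity. If leavers give no IS patients, the standard error of the phase effect rises by about 4 to 9%. The within-clinician estimate applies to clinicians with patients in both phases, which is why the all-clinician estimate should stay in the report.

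### The stated 33% clinician-attrition tolerance does not follow from the plan's own 384 and 288 patients; on those figures it is 25%

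*Protocol article*

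**What the plan says.** All the relevant figures stand in one paragraph of the protocol article, under Sample size justification and power calculations.

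- **Requirement.** Power "is .80 in a two-sided test, using repeated measures, with an alpha-level of 0.05", with "a standard deviation (sd) of 7 points (based on prior research", is given "for a sample size during the IS phase of 288 patients (144 per condition) within 32 clusters".
- **Planned enrolment.** The authors write that "we expect to randomize 32 clinics, with an average of three clinicians per clinic and at least four patients per clinician". The Summary of the proposed project agrees: 48 clinicians and 192 patients in each condition.
- **Full participation.** "Full participation in the IS and follow-up would yield 384 patients", with at least 1536 observations.
- **Tolerance.** As a direct consequence of these figures, "we could see a clinician attrition rate of 33% while remaining adequately powered to detect non-inferiority of CQI". The same sentence extends the claim to superiority of the implementation strategies over the baseline data.
- **Reassurance.** The next sentence says that this projection is higher than the attrition in the authors' prior studies in these systems. The prior rate is not given.

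Patient-level dropout and missing data are handled separately, by assuming four observations per patient on average. The 33% therefore concerns clinicians only.

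**The concern.** An attrition tolerance is the share of the enrolled number that can be lost before the required number is reached. Here 96 of 384 patients can be lost, which is a quarter. The plan says a third.

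The figure matters because the section expects substantial attrition and because this is its only numerical limit on clinician loss. The claims of adequate power for the non-inferiority comparison and for superiority over no intervention are both attached to it. The comparison with earlier attrition depends on it too. If the earlier rate lay between 25% and 33%, that reassurance would fail once the figure is corrected. The article does not allow the reader to tell.

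**Working it through.** **Inputs, all from the sample size section:** 32 clinics; 3 clinicians per clinic; 4 patients per clinician; 288 patients for power .80; two-sided alpha 0.05; margin 5 points; SD 7; clinic ICC 0.12; design effect up to 2.32. All 384 patients are granted to the comparison, which is the reading most favourable to the plan.

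**1. Reproduce the plan's totals.**
- Patients: 32 x 3 x 4 = 384. Agrees.
- Observations: 384 x 4 = 1536. Agrees.

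**2. Patients left after the stated loss.**
- One third of 96 clinicians is 32, so 64 remain: 64 x 4 = 256.
- At exactly 33%: 384 x 0.67 = 257.
- Shortfall against 288: 31 to 32 patients (32/288 = 11%), or 8 clinicians' worth.

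**3. Loss that leaves 288.**
- 1 - 288/384 = 0.25, or 24 of 96 clinicians. Check: 72 x 4 = 288.

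**4. Where 33% could come from.**
- (384 - 288)/288 = 96/288 = 33.3%. This matches the printed figure, with the requirement as denominator.
- To lose a true third and keep 288, full participation would have to be 288/(2/3) = 432.

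**5. Power at 256, calibrated to the plan's .80 at 288.** Power = Phi(2.802 x sqrt(r) - 1.960), where r is the effective sample size at 256 divided by that at 288. Design effect = 1 + (m - 1) x 0.12, with m patients per clinic: 2.32 at m = 12 (384/32), 1.96 at m = 9 (288/32), 1.84 at m = 8 (256/32).

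| Design effect at 288 | Design effect at 256 | r | Power at 256 |
|---|---|---|---|
| any fixed value | same value | 256/288 = 0.889 | .75 |
| 1.96 | 1.84 | 139.1/146.9 = 0.947 | .78 |
| 2.32 | 1.84 | 139.1/124.1 = 1.121 | .84 |

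**6. Is 288 itself a firm minimum?**
- Per arm without clustering: 2 x 2.802² x 7²/5² = 30.8, so 31. Times 2.32 = 71.9, so 72 per arm and 144 in total. This does not give 288.
- With the variance doubled, as for a change score with uncorrelated time points (an assumption; the article does not state it): 61.5, so 62 per arm. Times 2.32 = 143.8, so 144 per arm and 288 in total. This matches.

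So 288 can be reproduced, but only with an unstated variance assumption. The check of the tolerance does not depend on it, because the plan itself names 288 as its benchmark.

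**The case against.** The best case for the 33% has four parts.

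**Smaller clusters.** The printed design effect of 2.32 is the value at 12 patients per clinic. If it was used to obtain 288, and clinician loss then reduces each clinic to about 8 patients, the design effect falls to 1.84 and power at 256 is about .84. On that reading the trial is adequately powered at 33% attrition. This stands as a limit on the consequence. It does not rescue the sentence, which derives 33% from 384 and 288 without any argument about cluster size.

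**Leavers who treat patients first.** With one patient on average from each of 32 leavers, 64 x 4 + 32 = 288. This is plausible, since a clinician who leaves late in a one-year intervention phase may already have treated patients. The article does not state such a yield.

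**Larger enrolment.** The Recruitment section plans 3–4 clinicians per clinic, and four patients per clinician is given as a minimum. With 3.375 clinicians per clinic, or 4.5 patients per clinician, losing a third leaves exactly 288. This also stands as a possibility, so it would be too strong to say that 33% can hold only if every leaver contributes a patient. But the plan draws its 33% from 384, which uses 3 and 4.

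**Another origin for the figure.** Losing one of three clinicians in a clinic is also 33%. A reader might infer from the match with 96/288 that the wrong denominator was used. The documents do not show how the figure was reached, so that remains a likely explanation and no more.

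**Conclusion.** The stated tolerance is wrong on the plan's own figures. With 384 patients at full participation, 288 required, and no patients from clinicians who leave, the tolerance is 25% (24 of 96 clinicians). At 33% the trial would have about 256 patients, 32 below its benchmark.

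A reader might infer that the trial would be underpowered at 33% attrition. The documents do not support that as a firm conclusion. Calibrated to .80 at 288, power at 256 runs from about .75 to about .84, and the article does not say which design effect was used at 288. Whether 288 is a true minimum also depends on a variance assumption that it does not state.

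A reader might also infer that attrition would be monitored against the 33% line, or that this figure is the plan's only protection against turnover. The article describes no such monitoring rule, and it does mention incentives and system support. The point is a correction to one figure on which a power claim rests. The margin, the analysis and the enrolment target are not affected.

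**What to change.** Any one of these would make the sentence correct:

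- Replace 33% with 25% (24 of 96 clinicians).
- Keep 33% as the planning scenario, state the power at 256 patients, and name the design effect used at 288 and at 256.
- Keep 33% and state what makes it hold: an average of one patient from each departing clinician, or a full enrolment of about 432 patients (for example 4.5 per clinician).

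Then recheck the statement that this projection exceeds earlier attrition against the corrected figure, preferably giving the earlier rate.

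The cost is one figure or one sentence. The first two options, and stating a yield per leaver, need no extra patients. Relying on larger enrolment would commit the trial to about 48 patients beyond 384. The drawback of the 25% figure is that the stated safety margin becomes less favourable.
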